# 6. ANALYSES

## 6.1. Data analysis

### 6.1.1. Interim monitoring

No interim analysis will be performed, because we anticipate that the recruitment will be on-going over the course of the first 9 months and we will have recruited half of the planned sample size before we have any outcome data at all from the 4-month follow-up to review.

### 6.1.2. Preliminary Analyses

Our first set of analyses will check for out-of-range values and logical inconsistencies (someone reports on one question that he/she missed no days work in the prior month and then reports on a subsequent question that he/she missed 4 days in last month due to illness).

We will also compute summary statistics (mean, standard deviation, minimum, maximum, skewness) for each of our outcome variables and do a histogram plot to get a graphical picture of the distribution for each outcome. We will do this separately for outcomes at baseline, month 4, and month 15.

### 6.1.3. Analyses of Baseline Data

For continuous and ordinal variables, such as BD12 and HPQ, we will compute the means for the control and intervention groups and test whether they are significantly different using a t-test. For all yes/no baseline variables, we will compute the percentage yes in each of the two groups and compare using a 1 degree of freedom chi-square test. We may or may not report the p-values from these tests in our "Table 1", which will compare the groups at baseline. Whether or not we report them will depend on the journal that we submit the main outcome paper to since some journals want them reported and some do not.

### 6.1.4. Analyses of Primary Outcomes

Our two primary outcomes are the BD12 measure of depression severity and the HPQ measure of effective hours worked, both assessed at the month 4 follow-up. Both of these measures are continuous/ordinal variables so will compute the mean BD12 and mean HPQ at month 4 in the two groups, control and intervention.

We will first do unadjusted analyses to compare the means using a t-test. We will then do several adjusted analyses. First will use ANCOVA to compare the month 4 means on the outcome adjusting for baseline differences on the outcome. ANCOVA is simply another term for regression. For example, in one model, BD12 at month 4 will be the outcome and treatment group (a 0/1 variable) and baseline BD12 will the independent variables. These ANCOVA analyses provide estimates of "adjusted" month 4 group means as well as estimates of the adjusted difference in the group means (along with a p-value and confidence interval for the difference).

We will also do adjusted analyses which control for additional baseline variables, including variables which differ significantly between the control and intervention groups and variables which are strong predictors of the outcome under analysis. We will compare the estimated difference in group means and p-values to those obtained from the unadjusted analysis and the ANCOVA analyses which adjusts only for the baseline value of the outcome.

These analyses will be restricted to subjects who complete the month 4 follow-up (all of the statistical methods described above drop from the analysis those with a missing value on the outcome). Since a true intent-to-treat analysis estimates treatment effects based on data from all randomized subjects, not just those who complete a given follow-up, we will also do some mixed-model hierarchical linear models (HLM) to estimate treatment effects based on all subjects. NOTE: If the response rate is high at the month 4 follow-up (say at least 90%), bias due to missing data will likely be quite small and these analyses may not be necessary.

If it is necessary to do a HLM analysis, we will use what is called a mixed-model random coefficient model. Subjects are "random effects" with varying intercepts (baseline values) and vary slopes (rates of change from baseline to month 4). The dataset is structured so that each person has up to 2 records: one for baseline and one for follow-up. Even subjects who complete only the baseline enter into the analysis and are taken into account when estimating the month 4 mean in each group. For example, if subjects who do not complete the month 4 follow-up have higher baseline BD12 scores than subjects who do complete the month 4 follow-up, then the estimates of the month 4 means in this analysis will be higher than in the respondent only analyses described above. Such a model can be fit in SAS and other standard statistical packages such as STATA and SPSS.

For example, the random-coefficient ANCOVA model for BD12 would be:

BD12month4 = intercept + Beta1*treatment + Beta2 * BD12baseline

where the intercept and Beta2 parameters are modeled as random effects. Beta1 is a fixed effect and estimates the difference in the means in the intervention and control groups (i.e. estimates the treatment effect).

If conclusions based on the respondent-only and the intent-to-treat analyses are different, we will report intent-to-treat results.

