## 3.2. Sample size assumptions and estimates

A systematic review of psychological treatments, mostly CBT, for subthreshold depression yielded a Cohen’s d of 0.42 (95%CI: 0.23 to 0.60) at post-test and 0.16 (95%CI: 0.02 to 0.35) at 1-year follow-up (Cuijpers et al., 2007). ( a Cohen's d of .42 indicates a treatment effect (difference between control mean and intervention mean on the outcome measure) equal to 0.42 standard deviations (where standard deviation(SD) of interest if the SD of the outcome measure)

|  |  |  | 1:1 |  | If 1:2 |  | If 1:3 |  |
| --- | --- | --- | --- | --- | --- | --- | --- | --- |
| alpha | power | Effect size | n in each cell | Total N | n in active treatment | Total N | n in active treatment | Total N |
| 0.05 | 0.90 | 0.4 | **131** | 262 | **99** | 297 | **88** | 350 |
| 0.05 | 0.80 | 0.4 | **98** | 196 |  |  |  |  |

Thus, if we randomize 99 in the intervention group and twice that many in the control group (198) for a total of 297 randomized, we will have 90% power to detect a treatment effect assuming that this difference is equal to .40 standard deviations. However, these calculations ignore dropout. We expect that 90% will complete our month 4 followup, resulting in 89 respondents in the intervention group and 178 respondents at month 4 in the control group. In this situation, we will have 90% power to detect an effect size equal to .42 SD, which is exactly equal to our best estimate of what effect we expect to see at month 4 in this trial.

At month 15, we will have inadequate power to detect treatment effects since we expect those effects to be much smaller than those seen at month 4 (only about .16 SD's). However, in order to obtain insight into the next RCT to demonstrate prophylactic effect, we will conduct 15-month follow-up. Analyses of the 15-month follow-up will be exploratory.

If we think we can recruit 300 participants, we will go for 1:2 (intervention: control) allocation. If we expect to get closer to 200 total subjects only, we will go for 1:1 allocation, because the number in the active arm is important for journal reviewers and we would then not have 100 in the intervention group under 1:2 randomization.

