### 3.3.4. Intervention allocation

We will randomize eligible subjects to intervention and control groups at a ratio of 1:2. Randomization will be stratified on three variables, namely depression severity at baseline (BDI2=<19 vs >=20), absolute presenteeism prior to baseline (6 or higher vs 5 or lower, based on the obtained median of the eligible subjects in the pilot run) and center (Office X, Factory Y, Factory Z). Assuming that subjects are recruited from 3 sites, there will be a total of 12 strata. The study statistician will prepare 12 lists of random assignments ahead of time, one for each of the 12 strata. Each list will be blocked to ensure that the ratio of intervention to control is exactly 1:2 at set intervals within each stratum. The statistician will send these lists to the research assistant who is not involved in any other aspects of the study and who will build a spreadsheet that enables concealed sequential allocation and will be responsible for keeping these lists in the safe place.

Before randomizing an individual, the CRC will make a final determination of whether or not the person is eligible to be in the randomized trial. For example, prior to randomization, we will exclude those who score too low (BDI2=<9), which may well occur because of the difference between K6 and BDI2 and due to time elapsed for screening, because those who score too low at baseline will have less room for improvement. Once the CRC determines the eligibility of the participant, she will enter his/her registration number and the stratification variables to the spreadsheet which will automatically generate the allocation according to the pre-determined random sequence. The entered variables cannot be undone in order to guarantee allocation concealment.

Those randomized to control group will be put on a waiting list and after 15 months can receive the telephone CBT if they wish to do so.

One stratification factor is BDI2>=20 and BDI2<=19. This cutoff was chosen because our previous study suggests the score ranges 14-19 to be mildly ill, 20-28 to be moderately ill and 29- to be severely ill (Hiroe et al., 2005) and because our pilot study suggested that this is about the median BDI2 value for employees with K6>=9.

Another stratification factor is presenteeism, because this will be one of our primary outcomes and it is important to make sure that some effect can be seen, when in fact there is, probably among the more disturbed people.

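### Three kinds of respondent analysis are listed for each primary outcome, none is named as decisive, and one takes its covariates from the data

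*Protocol*

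**What the plan says.** Section 2.1 makes BDI2 and HPQ at month 4 the two outcomes on which effectiveness is decided. Section 6.1.4 (Analyses of Primary Outcomes) then describes the comparison: "We will first do unadjusted analyses to compare the means using a t-test. We will then do several adjusted analyses".

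The adjusted analyses are of two kinds:
- an ANCOVA on treatment and the baseline value of the same outcome;
- models with additional baseline variables, "including variables which differ significantly between the control and intervention groups and variables which are strong predictors of the outcome under analysis".

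Estimates and p-values from these are to be compared with one another. All three kinds use month-4 respondents only. A mixed model on all randomised subjects follows, but may be dropped if response is about 90% or better. If respondent-only and intent-to-treat conclusions differ, the intent-to-treat result is reported. No other order of precedence is given.

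On allocation, section 3.3.4 says: "We will randomize eligible subjects to intervention and control groups at a ratio of 1:2". It adds: "Randomization will be stratified on three variables, namely depression severity at baseline", followed by absolute presenteeism and center, which makes 2 × 2 × 3 = 12 blocked strata.

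**The concern.** An efficacy decision needs one test per outcome. Here three kinds of respondent analysis produce a p-value, and nothing says which counts when they disagree. The one precedence rule does not rank them. Section 3.2 expects 90% response, the very level at which the mixed model may be skipped, and then that rule does not operate at all.

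The third kind of model cannot be written down before the data are seen. Under randomisation, a significant baseline difference between arms is a chance event. Strength of association with the outcome can only be observed once month-4 data are in. No threshold is set for either criterion. The trial is non-blinded, so the discretion would be used by people who may know the allocation.

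The models also sit loosely with the randomisation. The t-test includes none of the three factors. The BDI2 ANCOVA carries continuous baseline BDI2 but names neither presenteeism nor center. The HPQ ANCOVA carries baseline HPQ but names neither BDI2 nor center. An analysis that ignores prognostic factors balanced by design overstates its standard error.

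**Working it through.** **1. The plan's own power (section 3.2).** Inputs: "we will have 90% power to detect a treatment effect assuming that this difference is equal to .40 standard deviations" with 99 and 198 randomised; then "We expect that 90% will complete our month 4 followup, resulting in 89 respondents in the intervention group and 178 respondents" and "we will have 90% power to detect an effect size equal to .42 SD". With two-sided alpha 0.05 (the sides are not stated, but two-sided reproduces the figures), power = Φ(d / √(1/n₁ + 1/n₂) − 1.96).
- 99 vs 198, d = 0.40: 0.40 × √66 = 3.250; Φ(1.290) = 0.901.
- 89 vs 178, d = 0.42: 0.42 × √59.33 = 3.235; Φ(1.275) = 0.899.

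Both match the stated 90%. The sample size is therefore that of an unadjusted comparison.

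**2. Power with own-baseline ANCOVA.** The residual SD becomes √(1 − r²), where r is the baseline-outcome correlation. The protocol gives no r, so a range is assumed. Power = Φ(3.235 / √(1 − r²) − 1.96):
- r = 0.3: Φ(1.431) = 0.924
- r = 0.5: Φ(1.776) = 0.962
- r = 0.6: Φ(2.084) = 0.981
- r = 0.7: Φ(2.570) = 0.995

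**3. The t-test under stratified allocation.** If the strata explain a share R² of the outcome variance, the t statistic has an SD of about √(1 − R²) instead of 1. A median split of a normal baseline explains 2r²/π. Assume also a center effect with SD 0.15, which adds 0.0225. True size = 2[1 − Φ(1.96 / √(1 − R²))]; power = Φ(1.275 / √(1 − R²)).
- r = 0.3: R² = 0.080, size 4.1%, power 90.8%
- r = 0.5: R² = 0.182, size 3.0%, power 92.1%
- r = 0.6: R² = 0.252, size 2.4%, power 93.0%
- r = 0.7: R² = 0.334, size 1.6%, power 94.1%

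**4. Simulation of the choice among models.** There were 267 completers, 12 strata and 1:2 blocks of 6, with 4,000 null runs and 1,500 runs at d = 0.42 for each r. Assumptions: block size; center SD 0.15; ten candidate covariates, three weakly prognostic (0.25, 0.20, 0.15), plus the other outcome's baseline; a covariate enters if its baseline p is below 0.05 or its absolute correlation with the outcome exceeds 0.2.

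| | r = 0.3 | r = 0.5 | r = 0.6 | r = 0.7 |
|---|---|---|---|---|
| **Type I error** | | | | |
| t-test | 4.20% | 3.18% | 2.53% | 1.92% |
| Own-baseline ANCOVA | 4.60% | 4.65% | 4.65% | 4.50% |
| Data-picked model | 4.45% | 4.32% | 4.05% | 3.75% |
| ANCOVA with own baseline, other baseline and center | 4.85% | 4.82% | 4.92% | 5.00% |
| Any of the first three significant | 6.38% | 6.70% | 6.62% | 6.42% |
| **Power at d = 0.42** | | | | |
| t-test | 91.4% | 91.9% | 92.4% | 92.9% |
| Own-baseline ANCOVA | 93.8% | 97.2% | 99.0% | 99.7% |
| ANCOVA with own baseline, other baseline and center | 94.1% | 97.3% | 99.0% | 99.7% |

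The Monte Carlo standard error of the any-of-three rate is √(0.065 × 0.935 / 4000) = 0.39 points. Other assumed covariates under the same stratified design gave 5.6% to 6.8%. Simulated ANCOVA power runs up to 1.4 points above the formula in step 2, with a standard error of at most about 0.6 points. I rely on the formula for level and on the simulation for differences between models.

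**The case against.** Much of the opposing case stands.

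- **The factors are not absent from every model.** A reader might infer that they are, but each ANCOVA adjusts for the continuous baseline of its own outcome, and the mixed-model formula contains baseline BDI2. Continuous BDI2 holds more information than its split at 19/20. The list of extra covariates is also open, so center is unnamed and not excluded.
- **The planned 90% power is not at risk.** A reader might infer lost power because the t-test comes first. First is an order of work and not a designation, and section 3.2 sized the trial for an unadjusted comparison. Precision is forgone only if the t-test decides. Once own-baseline ANCOVA is used, the missing factors add at most 0.3 points.
- **Inflation does not approach 10%.** A reader might infer that from three tests. The models are highly correlated, and the t-test is conservative in this design. Simple instead of stratified allocation gives 7.3% to 8.2% (eight candidate covariates, r of 0.4 to 0.5), but that is not this trial.
- **No rule says that any significant result suffices.** Comparing estimates across models is how sensitivity analyses are normally used. The data-picked model on its own keeps its level (3.75% to 4.45%).
- **A statistical analysis plan may name the decisive model.** Naming it is commonly left to such a plan, so its absence here would be a weak point if it stood alone.

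What remains is that the protocol itself prescribes data-driven covariate selection, and sets it beside two other analyses for a decision that section 2.1 rests on these outcomes. That is stated text and not an omission.

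**Conclusion.** The point holds in a limited form. The primary comparison is left open among a t-test, an own-baseline ANCOVA and models with covariates picked after seeing the data. The single precedence rule does not settle the choice.

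If the choice were exercised in favour of significance, type I error per outcome would be about 6% to 7% instead of 5%. This rests on assumed covariates, selection thresholds and block size, and on a decision rule that the protocol never states. If the t-test were made decisive, the error would run the other way. The test would be conservative, with true size about 2% to 4%. It would forgo about 2 to 7 points of power against own-baseline ANCOVA in the simulation (93.8 − 91.4 = 2.4 at r = 0.3; 99.7 − 92.9 = 6.8 at r = 0.7). Leaving center and the other stratifier out of the ANCOVA has a negligible effect on power and makes the test slightly conservative (about 4.6% against 5%).

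The amounts are small, but they bear on the trial's efficacy decision and can be removed without cost. Multiplicity across the two primary outcomes is a separate matter and is not counted here.

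**What to change.** In section 6.1.4 (Analyses of Primary Outcomes), name one primary analysis per outcome: an ANCOVA of the month-4 value on treatment, the continuous baseline value of that outcome, and the randomisation factors. These are center, and the BDI2 and presenteeism strata where the continuous baseline does not already carry them. In the BDI2 model the BDI2 stratum is largely redundant. In the HPQ model, keep the presenteeism stratum unless absolute presenteeism and the effective-hours score prove to be the same quantity. The existing preference for intent-to-treat results can then apply to this one model, with the same covariates in the mixed model.

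Label the t-test and any extended model as supportive. Delete the selection of covariates by significant baseline difference or by observed association with the outcome. If an extended model is wanted, list its covariates in advance. Make the matching change in section 6.1.5 (Analyses of secondary outcomes), which repeats the same sequence.

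The cost is wording only. Every variable is already collected at screening, baseline or randomisation, and the sample size does not change.

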## 2.3. Subgroup hypotheses

The effectiveness of the program may differ according to the initial severity of depression. We will therefore use as one stratification factor high/low subthreshold depression, and analyze the results according to these a priori defined subgroups. Because we do not have enough sample size to have adequate power to detect if treatment effects vary significantly by subgroup (i.e. for subgroup hypotheses), these will be more exploratory (i.e. hypothesis generating) than definitive analyses. Although we will test for treatment by subgroup interactions, our focus will be descriptive, describing the pattern of treatment effects by subgroup. To reduce the number of these analyses, we will focus on our primary outcomes (BD12 and HPQ at month 4).

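### With 1:2 arms, the unqualified t-test and ANCOVA would be better specified as Welch and heteroscedasticity-robust; how much this matters depends on an SD ratio the protocol does not give

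*Protocol*

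**What the plan says.** Section 6.1.4 sets out the comparison of month 4 BDI2 and HPQ means: "We will first do unadjusted analyses to compare the means using a t-test". ANCOVA adjusting for the baseline value comes next, and the section explains that "ANCOVA is simply another term for regression". Treatment is a 0/1 regressor, and a p-value and confidence interval are promised for the adjusted difference. Further regressions add other baseline variables. Section 6.1.5 (Analyses of secondary outcomes) applies the same sequence to continuous and ordinal secondary outcomes.

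On allocation, section 3.3.4 states: "We will randomize eligible subjects to intervention and control groups at a ratio of 1:2". Section 3.2 keeps an alternative open: "If we expect to get closer to 200 total subjects only, we will go for 1:1 allocation".

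Section 3.2 works in units of one common SD, "assuming that this difference is equal to .40 standard deviations", and gives the expected numbers: "We expect that 90% will complete our month 4 followup, resulting in 89 respondents in the intervention group and 178 respondents at month 4". The protocol gives no SD by arm and no SD ratio, and it does not mention pooled, Welch, model-based or robust standard errors.

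**The concern.** The classical two-sample t-test estimates one variance from both arms, and ordinary regression estimates one residual variance. With equal arms this does almost no harm if the SDs differ. With 1:2 arms the control group supplies about two thirds of the variance estimate, while the smaller CBT arm contributes most of the uncertainty in the difference. If the CBT arm has the larger SD, the computed standard error is too small. If it has the smaller SD, the standard error is too large.

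A treatment whose effect varies between people generally changes the spread in the treated arm, and section 2.3 allows for this: "The effectiveness of the program may differ according to the initial severity of depression". Both primary outcomes share the exposure, and so do the confidence intervals, whether or not the mean effect is zero. The vulnerability comes from the 1:2 design, and the analysis section names no variance option in response to it.

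**Working it through.** **Inputs from the protocol.** Alpha 0.05 and power 0.90 (section 3.2 table; two-sided is inferred because it reproduces the table). 99 and 198 randomized, 89 and 178 respondents, effect sizes 0.40 and 0.42 SD (section 3.2).

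**Assumed.** The ratio r = CBT SD / control SD, varied because the protocol gives none; normal, independent observations; baseline correlation 0.5 for ANCOVA.

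**1. The plan's own figures.** The two-sided 1:2 formula gives n = 99 and 198 for 0.40 SD at 90% power, matching the protocol (power 0.901 by normal approximation, 0.900 by noncentral t). At 89 v 178 and 0.42 SD, power is 0.899 (normal) or 0.897 (t), matching the stated 90%.

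**2. Pooled t-test when SDs differ.** Set the control SD to 1, n1 = 89 and n2 = 178.

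- Pooled variance = (88r² + 177)/265
- Computed SE = √[pooled variance × (1/89 + 1/178)]
- True SE = √(r²/89 + 1/178)
- Large-sample type I error = 2 × [1 − Φ(1.969 × computed SE / true SE)]

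Example, r = 1.44: pooled variance 1.3565, computed SE 0.1512, true SE 0.1700, SE ratio 0.889, type I error 8.0%.

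Example, r = 0.74: pooled variance 0.8498, computed SE 0.1197, true SE 0.1085, SE ratio 1.103, type I error 3.0%.

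| r | Pooled, formula | Pooled, simulated | Welch, simulated |
|---|---|---|---|
| 0.75 | 3.1% | 3.1% | 4.9% |
| 0.80 | 3.4% | 3.5% | 5.0% |
| 0.90 | 4.1% | 4.2% | 5.0% |
| 1.00 | 4.9% | 5.1% | 5.1% |
| 1.10 | 5.7% | 5.8% | 5.0% |
| 1.25 | 6.7% | 6.7% | 4.9% |
| 1.50 | 8.4% | 8.4% | 5.0% |

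Simulations used 100,000 runs per ratio. In the same formula with equal arms (100 v 100), the pooled test gives 4.9% at every ratio from 0.5 to 2.

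**3. ANCOVA at 89 v 178** (20,000 runs per ratio, r applied to the residual SD).

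| r | Model-based errors | HC3 errors |
|---|---|---|
| 0.75 | 3.2% | 5.0% |
| 1.00 | 5.1% | 4.9% |
| 1.25 | 7.1% | 5.2% |
| 1.50 | 8.6% | 4.9% |

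**4. Cost when the SDs are equal** (0.42 SD, 89 v 178). t-test power is 89.4% pooled v 89.3% Welch. ANCOVA power is 96.3% with model-based errors v 96.2% with HC3.

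**5. Which ratios are plausible?**

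- If individual effects are independent of the untreated score, r = √(1 + effect SD²). Suppose half the clients gain nothing and half gain 0.84 SD (mean 0.42). The effect SD is 0.42, r = √1.1764 = 1.085, and the pooled error is 5.5%.
- Reaching r = 1.3 needs an effect SD of √0.69 = 0.83. Reaching r = 1.44 needs √1.0736 = 1.04.
- If instead the 0.84 SD gain goes only to clients above median baseline severity, the CBT variance is 1 + 0.1764 − 2 × 0.84 × 0.5 × 0.399 = 0.841. Then r is about 0.92 and the pooled error about 4.3%.
- A simulation of ANCOVA with effects varying by baseline severity gave 4.9% to 5.5%.

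**The case against.** The strongest objection is that the protocol never says the variance is pooled. Welch's test is a t-test, and regression with robust errors is still regression, so both fit section 6.1.4 as written. Such options are often left to an analysis plan, and one may exist. This stands: the equal-variance reading is an inference from common software defaults. A reader might infer that the protocol plans a wrong standard error, but the text does not support that.

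A reader might also infer that the trial's false-positive rate will be 3% to 8%. The documents do not support that either. The range needs SD ratios of about 0.74 to 1.44, and the protocol's own effect size makes the upper end hard to reach (step 5 of the working). If CBT changes nobody's outcome, randomization gives both arms the same distribution and the error stays near 5%. Inflation therefore needs a zero mean effect together with a wider spread, meaning some clients helped and others harmed.

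Section 2.3 gives little support for inflation. It says only that effectiveness may differ by severity and treats the question as exploratory. Section 3.3.4 suggests the effect may show mainly in more disturbed participants, which would tend to narrow the CBT arm and make a pooled test mildly conservative.

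What remains is that an unqualified t-test and regression are ordinarily run with equal-variance errors. At 1:2 those are calibrated only if the spreads match, and the alternative costs almost nothing.

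**Conclusion.** This is a low-cost improvement and does not correct a misstatement. If the default reading applies at 89 v 178, type I error is about 4% to 6% with arm SDs within 10% of each other. It is about 3% at an assumed ratio of 0.74 and about 8% at 1.44. It is inflated only when the CBT arm has the larger SD; when it has the smaller SD the test is conservative and some power is lost. Interval coverage shifts in the same way whenever CBT changes the spread, even if the mean effect is real. The problem disappears if CBT affects no one, or if the 1:1 option in section 3.2 is used.

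These sizes rest on normal, independent data, a two-sided 5% test, a baseline correlation of 0.5 for ANCOVA, and SD ratios that the documents do not supply.

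**What to change.** In section 6.1.4, and in section 6.1.5 on secondary outcomes, name the Welch (unequal-variance) t-test for the unadjusted comparisons. Name heteroscedasticity-robust standard errors, for example HC3, for the ANCOVA and the further adjusted regressions of continuous outcomes. Fixing this in advance also removes any choice between versions after the SDs have been computed under section 6.1.2.

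The cost is one sentence, no participants and no data, and about 0.1 point of power if the SDs are equal.

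The change should not be carried over to the mixed model in 6.1.4 as arm-specific residual variances. With a random intercept, a random slope and at most two records per person, the residual variance is already not separately identifiable. Two records yield two variances and one covariance, whereas the model has two random-effect variances, their covariance and a residual variance.
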